## Abstract

**Introduction:**

COVID-19 has spread rapidly worldwide, causing significant morbidity and mortality. People from ethnic minorities, particularly those working in healthcare settings, have been disproportionately affected. Current evidence of the association between ethnicity and COVID-19 outcomes in people working in healthcare settings is insufficient to inform plans to address health inequalities.

**Methods and analysis:**

This study combines anonymised human resource databases with professional registration and National Health Service data sets to assess associations between ethnicity and COVID-19 diagnosis, hospitalisation and death in healthcare workers in the UK. Adverse COVID-19 outcomes will be assessed between 1 February 2020 (date following first confirmed COVID-19 case in UK) and study end date (31 January 2021), allowing 1-year of follow-up. Planned analyses include multivariable Poisson, logistic and flexible parametric time-to-event regression within each country, adjusting for core predictors, followed by meta-analysis of country-specific results to produce combined effect estimates for the UK. Mediation analysis methods will be explored to examine the direct, indirect and mediated interactive effects between ethnicity, occupational group and COVID-19 outcomes.

**Ethics and dissemination:**

Ethical approval for the UK-REACH programme has been obtained via the expedited HRA COVID-19 processes (REC ref: 20/HRA/4718, IRAS ID: 288316). Research information will be anonymised via the Secure Anonymised Information Linkage Databank before release to researchers. Study results will be submitted for publication in an open access peer-reviewed journal and made available on our dedicated website (https://uk-reach.org/).

**Trial registration number:**

ISRCTN11811602.

Strengths and limitations of this studyFirst large UK-wide study assessing the associations between ethnicity and COVID-19 outcomes in people who work in healthcare settings.Ambitious linkage of multiple anonymised human resource and professional registration databases with National Health Service data sets, aiming to provide coverage of the whole of the UK.Broad and comprehensive analysis that aims to unpick the associations between ethnicity, occupational group and multiple COVID-19 outcomes while adjusting for core predictors.Access to highly detailed human resource databases (including Electronic Staff Record for England and Wales) enables granular analyses of ethnicity, occupation and COVID-19 exposures.While every effort has been made to identify as many healthcare workers as possible, the lack of a single UK-wide database capturing those actively working within healthcare settings is a key limitation that may reduce our ability to identify all healthcare workers across all regions.

## Introduction

COVID-19 has been declared a global pandemic. Since the first reported cases in December 2019, over 110.7 million cases and 2.4 million deaths have been reported worldwide.^1^ Consistent evidence identifies advanced age, male sex, socioeconomic deprivation and chronic comorbidities as core predictors for COVID-19 adverse outcomes.^2–5^

The COVID-19 pandemic has disproportionately impacted historically disadvantaged populations.^6^ In the UK, higher infection and mortality rates are observed in areas with greater deprivation^7^ and among ethnic minorities.^8–12^ This has prompted calls to prioritise the publication of data disaggregated by ethnicity and to conduct research which increases our understanding of risk in these populations.^13 14^ Ethnicity is a complex construct which represents social, biological or genetic differences between populations.^15^ Potential explanations for COVID-19-related health disparities between ethnic groups include socioeconomic, cultural, behavioural, biological or pathophysiological differences.^16^ It is recommended that investigations into ethnicity-related health inequality should also consider interrelated factors such as deprivation, religion and pre-existing conditions. This approach serves to highlight the interplay between ethnic disparities and economic inequality^13^ and disentangle the independent importance of these factors.^14^

Those working in healthcare settings, hereafter referred to as Healthcare Workers (HCWs), have a greater risk of SARS-CoV-2 exposure and transmission due to the number of COVID-19 cases requiring medical intervention.^17^ A Scottish linkage study concluded over a sixth of hospitalised COVID-19 cases were HCWs or members of their households.^18^ There is concern that HCWs from ethnic minority groups are at increased risk of adverse outcomes from COVID-19. However, the interplay between ethnicity and healthcare occupation and its impact on COVID-19 outcomes is unclear. Publicly available data indicate that individuals from ethnic minorities account for 65%–76% of deaths reported in clinical HCWs, despite contributing less than 20% of the National Health Service (NHS) workforce.^19 20^ We must understand differences in risks in these populations to protect the most vulnerable HCWs and maintain a functioning healthcare system.^18^ However, the quality of data available to evaluate COVID-19 outcomes in HCWs, and the impact of ethnicity on these outcomes, remains poor and limited by small sample size.

The United Kingdom Research study into Ethnicity And COVID-19 diagnosis and outcomes in Healthcare workers (UK-REACH) programme will rapidly examine differences in COVID-19 diagnosis, clinical outcomes, professional practices and well-being among HCWs from different ethnicities. It will provide rapid evidence through five interlinked work packages; a large data linkage cohort study, a longitudinal cohort study, a legal/ethical analysis, a qualitative work stream and the development of a stakeholder working group. Here we describe the protocol for the large data linkage cohort study, which will bring together anonymised human resource (HR), professional registration and NHS data sets within a Trusted Research Environment.^21^ This linked database will be used to assess the relationship between ethnicity and COVID-19 diagnosis, hospitalisation and death in HCWs.

### Objectives

Our primary aim is to determine whether COVID-19 diagnosis, hospitalisation and mortality rates differ between ethnic and occupational groups in HCWs. We will conduct both a broad analysis, encompassing all those registered as HCWs on 1 February 2020 in the UK, and a detailed substudy analysis in those actively working during the COVID-19 pandemic, incorporating more granular ethnicity, occupation and exposure information.

Considering current evidence, we hypothesise that HCWs from ethnic minority backgrounds will have increased risk of COVID-19 diagnosis and adverse outcomes compared with their White counterparts regardless of occupation.

## Methods

### Study design

We will use data from multiple linked electronic health record (EHR) databases to investigate the study hypotheses within a cohort of HCWs. The cohort study will begin on 1 February 2020 (date following first confirmed COVID-19 case in UK) and follow participants for 1 year, until 31 January 2021.

### UK healthcare data sources

For all residents in the UK, healthcare is free at the point of delivery as part of the Government-funded NHS. The NHS employs around 1.6 million people in hospital and community health services; over half are professionally qualified clinical staff (including doctors, nurses, midwives, technical and ambulance staff), the remainder support clinical staff and the NHS Infrastructure. However, identification of all HCWs in the UK is not straightforward. There is no single UK-wide database capturing these employees as the health systems in England, Scotland, Wales and Northern Ireland have diverged since political devolution in 1999. Further, many staff groups that provide NHS services, including general practitioners (GPs) and dentists, are not directly employed by the NHS.

Our primary data sources for identifying HCWs are the NHS HR and payroll databases, namely the Electronic Staff Record (ESR), capturing approximately 1.4 million staff paid through the NHS in England and Wales, and the Scottish Workforce Information Standard System (SWISS) including approximately 170 000 staff directly employed by NHS Scotland; as well as clinical staff, these databases include NHS paid ancillary and administrative services staff, and those in management roles. These HR databases cover NHS organisations including hospital trusts, ambulance services and clinical commissioning groups with comprehensive employment data during the cohort period of interest (table 1). We also aim to access HR data from non-NHS ancillary worker contractor companies to capture non-clinical staff and those working in facilities management and care coordination positions.

**Table 1 T1:** Coverage of human resources and professional registration databases utilised to identify UK healthcare worker cohort for the planned study

Registry	Approximate size	Country coverage	Occupational coverage
Electronic Staff Record (ESR)	1.4 million	England and Wales*	Staff directly employed by NHS England and Wales.
Scottish Workforce Information Standard System (SWISS)	163 k	Scotland	Staff directly employed by NHS Scotland.
General Medical Council (GMC)	336 k	England, Wales, Scotland and Northern Ireland	All doctors.†
Nursing & Midwifery Council (NMC)	706 k	England, Wales, Scotland and Northern Ireland	Nurses, midwives, student nurses and nursing associates.‡
General Dental Council (GDC)	110 k	England, Wales, Scotland and Northern Ireland	Dentists, dental care professionals and dental practices.§
General Optical Council (GOC)	30 k	England, Wales, Scotland and Northern Ireland	Optometrists, dispensing opticians, student opticians.
General Pharmaceutical Council (GPhC)	94 k	England, Wales and Scotland	Pharmacists and pharmacy technicians.
Pharmaceutical Society Northern Ireland (PSNI)	3 k	Northern Ireland	Pharmacist and trainee pharmacists.
Health and Care Professions Council (HCPC)	280 k	England, Wales, Scotland, Northern Ireland and international¶	Art therapists, biomedical scientists, chiropodists, podiatrists, clinical scientists, dietitians, hearing aid dispensers, occupational therapists, operating department practitioners, orthoptists, paramedics, physiotherapists, practitioner psychologists, prosthetists, orthotists, radiographers, speech and language therapists.

*Two foundation trusts in England do not currently use ESR.

†Including those in UK Foundation Year 1 and 2 posts, general practitioners and specialist consultants.

‡In England only.

§Dental care professionals include clinical dental technicians, dental hygienists, dental nursed, dental technicians, dental therapists, orthodontic therapists.

¶International professionals will not be included in this study as linkage to electronic health records, thus assessment of outcomes will not be possible.

To enable wider coverage of the UK and capture workers in non-NHS sectors (eg, community and primary care), the HR data will be supplemented by health and social care regulators, where available. These include the General Medical Council (GMC), Nursing and Midwifery Council (NMC), General Dental Council (GDC), General Pharmaceutical Council (GPhC), General Optical Council (GOC), Pharmaceutical Society Northern Ireland (PSNI) and Health and Care Professions Council (HCPC). Where possible, we will obtain data for all HCWs registered to these regulators on the cohort inception date (1 February 2020). As these registries provide less information on specific occupational role and workplace location, it is not possible to identify those actively working during the study period. All included bodies provide UK-wide coverage, except pharmaceutical bodies GPhC and PSNI, which regulate Great Britain and Northern Ireland separately. Table 1 compares the coverage, inclusion, and data available from each registration database.

Given the differences in coverage and data across databases, the analysis will be twofold. First, a broad analysis will address the main objective using the full UK-wide cohort for any HCW employed or registered on 1 February 2020. Second, a detailed HR substudy will incorporate additional information on ethnicity, occupational role and potential for SARS-CoV-2 exposure (including whether an individual actively worked during the study period), and changes to these throughout the study period.

COVID-19 diagnosis, hospitalisation and mortality data will be gathered from several routinely collected EHR databases. We aim to obtain primary and secondary care data sets as well as specific intensive care audit data (such as Intensive Care National Audit & Research Centre data for England and Wales and Scottish Intensive Care Society Audit Group data for Scotland) and mortality information (Office for National Statistics, ONS) for each country. We also plan to incorporate specialised COVID-19 related databases, including COVID-19 surveillance data (COVID-19 Hospitalisation in England Surveillance System, CHESS), COVID-19 Symptom Study app data,^22^ and Public Health England (PHE) Pillar 1 (within hospital) and Pillar 2 (community-based) testing data, where available. Additional data sets, such as PHE Pillars 3 and 4, will be sought and incorporated if obtained.

It may not be possible to access all outcome data sets for England, Wales, Scotland and Northern Ireland. Therefore, outcomes will be assessed separately in each country and results combined using meta-analysis methods to produce UK-wide estimates.

### Data linkage

Anonymised data will be stored at the Secure Anonymised Information Linkage (SAIL) databank.^21^ SAIL works in partnership with a trusted third party, the NHS Wales Informatics Service (NWIS), to ensure processing of personal data is kept within the NHS and separate from the research environment. The process for anonymisation and linkage is depicted in figure 1.

**Figure 1 F1:**
[figure not shown]
Data flow and linkage of UK-REACH data sources. The above diagram and style was interpreted from an initial data flow diagram created and provided by [name] at the University of Bristol. It has been repurposed and amended to illustrate data flows specific to the UK-REACH project by [name] at Swansea University. UK-REACH, United Kingdom Research study into Ethnicity And COVID-19 diagnosis and outcomes in Healthcare workers.

The process to create the cohort of HCWs is as follows: Information from the HR and regulator databases will be separated into identifiable data and other administrative data. The identifiable data will be sent directly to NWIS and anonymised by encrypting identifiers into a single anonymous ID. Databases will be linked using this ID to identify the study cohort of HCWs and duplicate information from individuals present in more than one of the HR and regulator databases will be removed. Other administrative data will be sent directly to SAIL, who will use the anonymous study ID (subsequently removed to prohibit reverse engineering of re-identification) to match to the anonymised data.

The process for obtaining linked healthcare records for the cohort is as follows: NWIS will share the identifiers from the study cohort with the relevant health record providers, such as NHS Digital, NHS Scotland and the Northern Ireland Honest Broker Service, to establish linkage to required data sets. The health record providers then return the linked health records, including information for outcomes and predictors, following the same split-file process (identifiable data to NWIS, anonymised data to SAIL). Identifiable health record data will be kept entirely within the NHS. Linked anonymised records will be matched in SAIL using the anonymous study ID to enable the project analysis. Once the linkage process is complete, the identifiable data will be deleted in accordance with the contractual arrangement between NWIS and SAIL.

We will develop a process to enable access to the UK-REACH data for other researchers once this study is complete. This process will engage with the above health record providers to establish onward sharing in partnership with the SAIL Databank.

### Study population

The cohort will include all adult (aged 16 years and over) HCWs captured by HR records or registered with at least one professional regulator on 1 February 2020, excluding those which linkage to EHRs is unsuccessful. HCWs with missing ethnicity, occupation, age, sex or postcode will be excluded from the main analysis. For the HR substudy, only those actively working will be included, thus excluding those on parental, sickness or disability leave for the duration of study period.

### Observation period

Follow-up commences on the index date (1 February 2020) (or date of return/commencement of employment for the HR substudy) and continue until either their death date (COVID-19 related or due to other causes) or the study end date (31 January 2021). For the HR substudy, those leaving NHS employment during the study period will be included up until this date, at which point they will be censored.

### Main exposures

The main exposure of interest is ethnicity, which is likely to be inconsistently recorded across databases. We will primarily assign ethnicity using staff HR records (ESR or SWISS) and registration databases (if not included/missing from HR records). If ethnicity is missing from these databases, linked EHRs will be assessed. Those with ethnicity recorded as ‘not stated’ or with completely missing ethnicity information will be excluded from the main analyses. Ethnicity will be categorised based on ONS groupings (table 2).

**Table 2 T2:** ONS ethnicity groupings

Broad ethnic categories	Ethnic groups
White	English/Welsh/Scottish/Northern Irish/British Irish Gypsy or Irish Traveller Any other White background
Mixed/multiple ethnic groups	White and Black Caribbean White and Black African White and Asian Any other mixed/multiple ethnic background
Asian/Asian British	Indian Pakistani Bangladeshi Chinese Any other Asian background
Black/African/Caribbean/Black British	African Caribbean Any other Black/African/Caribbean background
Other ethnic group	Arab Any other ethnic group

ONS, Office for National Statistics.

A more granular analysis will incorporate subdivisions of ethnicity (particularly within Asian/Asian British category) if a sufficient number of events are observed.

Occupational group (and its interaction with ethnicity) is also of primary interest. We will assign occupation for the main cohort using data recorded on 1 February 2020 from either HR records or data held by the regulating bodies and the following categories informed by version 17.1 of the NHS Occupational Code Manual (*NHS Digital*):

Ambulance staffAdministrations and estates staffHealthcare assistants and other support staffMedical staffDental staffNursing, midwifery and health visiting staffNursing, midwifery and health visiting learnersScientific, therapeutic and technical staffHealthcare sciencesGeneral payments

A more granular analysis will incorporate subdivisions of occupational groups (particularly the Medical staff group) if a sufficient number of events are observed.

### Outcomes

The main outcomes are COVID-19 diagnosis (confirmed and suspected, confirmed only), hospitalisation (all, COVID-19 specific, ITU admission) and mortality (all-cause, COVID-19 specific). The definitions, data sources and a summary of planned analyses for these outcomes are provided in table 3: COVID-19 outcomes and definitions, identified via listed data sources, to be assessed in UK HCW cohort and within listed subgroups, via listed analysis approach in the planned study.

**Table 3 T3:** COVID-19 outcomes and definitions, identified via listed data sources, to be assessed in UK healthcare worker cohort and within listed subgroups, via listed analysis approach in the planned study

Outcomes		Definitions	Data sources	Subgroups	Analysis approach (output)
COVID-19 diagnosis	Confirmed COVID-19 diagnosis	A positive swab test for SARS-CoV-2 during the study period	PHE Pillar 1 (PHE laboratories or NHS hospital) and Pillar 2 (wider population) testing data^1^		Poisson regression (IRR)
	Suspected COVID-19 diagnosis	Self-reporting of either a positive SARS-CoV-2 test or combination of symptoms shown to be predictive of positive testing^2^ during the study period or suspected case SNOMED CT codes (NHS Digital) recorded during the study period	COVID-19 Symptom Study app and primary care data		Poisson regression (IRR)
Hospitalisation	All hospitalisations	Any hospital admission recorded during the study period	Secondary care and CHESS data	Confirmed COVID-19 diagnosis	Logistic regression (OR)
	COVID-19 hospitalisations	hospital admissions with COVID-19-specific ICD-10 codes^3^ during the study period or positive swab test for SARS-CoV-2 recorded during or within 28 days prior to admission	Secondary care, CHESS, PHE Pillar 1 (PHE labs or NHS hospital) and Pillar 2 (wider population) testing data^1^	Confirmed COVID-19 diagnosis	Logistic regression (OR)
	COVID-19 ITU admissions	Admissions to ITU during the study period	Secondary care, CHESS, and intensive care audit data	Confirmed COVID-19 diagnosis	Logistic regression (OR)
Mortality	All-cause mortality	Any death registration recorded during the study period	ONS mortality, primary care and secondary care data	Confirmed COVID-19 diagnosis COVID-19 hospitalisations COVID-19 ITU admissions	Flexible parametric time-to-event regression (HR)
	Mortality due to COVID-19	any death registration with COVID-19-specific ICD-10 codes^3^ recorded for the primary or secondary cause of death during the study period	ONS mortality, primary care and secondary care data	Confirmed COVID-19 diagnosis COVID-19 hospitalisations COVID-19 ITU admissions	Flexible parametric time-to-event regression (HR)

*PHE Pillar 3 (serology testing for antibodies) and Pillar 4 (blood and swab testing) data will be incorporated if obtained.

†Symptoms include loss of smell or taste, fatigue, persistent cough and loss of appetite.^34^

‡COVID-19-specific ICD-10 codes are U07.1: ‘COVID-19, virus identified’ and U07.2: ‘COVID-19, virus not identified’.

CHESS, COVID-19 Hospitalisation in England Surveillance System; ICD-10, International Classification of Diseases—10th revision; IRR, incidence rate ratio; ITU, Intensive Therapy Unit; NHS, National Health Service; ONS, Office for National Statistics ; PHE, Public Health England; SNOMED CT, Systematised Nomenclature of Medicine Clinical Terms.

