### Outcome incidence

Adjusted annual and quarterly incidence rates, per 100 000 HCWs, for each outcome will be calculated for each country where available. Meta-analysis methods will combine the country-specific estimates to give an overall UK incidence rate estimate. Adjusted incidence rates by ethnicity and occupation will be calculated in the same way. All incidence rates will be adjusted for the four core predictors (age, sex, comorbidities and deprivation) using standardisation methods. The incidence rates of each outcome will be reported as the rate of cases in the final UK HCW cohort and within subgroups who have experienced preceding COVID-19 events (table 3: COVID-19 outcomes and definitions, identified via listed data sources, to be assessed in UK HCW cohort and within listed subgroups, via listed analysis approach in the planned study). The time between diagnosis and outcomes will be summarised and cumulative incidence curves will be plotted.

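### The broad diagnosis outcome (confirmed and suspected) has no route for hospital or death records coded U07.1 or U07.2, so some COVID-19 admissions and deaths count as never diagnosed

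*Protocol article*

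**What the plan says.** The Outcomes section names two versions of the diagnosis outcome: confirmed and suspected together, and confirmed only. Table 3 of the protocol article builds them and the later outcomes as follows.

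- **Confirmed diagnosis:** "A positive swab test for SARS-CoV-2 during the study period", from "PHE Pillar 1 (PHE laboratories or NHS hospital) and Pillar 2 (wider population) testing data". A footnote adds Pillars 3 and 4 if they are obtained.
- **Suspected diagnosis:** self-report of a positive test or of predictive symptoms, "or suspected case SNOMED CT codes (NHS Digital) recorded during the study period". The sources are "COVID-19 Symptom Study app and primary care data".
- **COVID-19 hospitalisation:** "hospital admissions with COVID-19-specific ICD-10 codes" in the study period, "or positive swab test for SARS-CoV-2 recorded during or within 28 days prior to admission". The swab is an alternative, not a requirement.
- **COVID-19 mortality:** a death registration carrying one of the same codes as primary or secondary cause. No swab is needed.
- **Accepted codes (footnote):** "U07.1: ‘COVID-19, virus identified", and U07.2, which the footnote glosses as virus not identified.

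The Outcome incidence section reports rates in the whole cohort and "within subgroups who have experienced preceding COVID-19 events". It also plans to summarise the interval from diagnosis to later outcomes.

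**The concern.** The broad diagnosis outcome is meant to be the sensitive one. The Discussion explains that suspected cases are included to capture more infections, at some cost in specificity. That outcome accepts symptoms entered in an app, but not an admission or a death that the study's own hospital or mortality data code as COVID-19. The cases left out are severe ones, already visible in sources planned for linkage.

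Two things follow. First, the broad diagnosis outcome does not contain the severe outcomes, so its incidence is too low by the number of such workers. Second, these workers have no diagnosis date, so the interval from diagnosis to hospitalisation or death is undefined for them. If the proportion lost differs by ethnic group, the ethnic contrast in diagnosis also shifts, and that contrast belongs to the study's primary aim.

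**Working it through.** **1. Table 3 compared row by row**

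| Record (no positive swab linked, no app report, no suspected-case GP code) | Confirmed | Suspected | COVID-19 hospitalisation | COVID-19 death |
|---|---|---|---|---|
| Admitted, coded U07.1 | no | no | yes | – |
| Admitted, coded U07.2 | no | no | yes | – |
| Died, U07.1 or U07.2 as a cause of death | no | no | – | yes |

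Neither diagnosis row lists an ICD-10 code, secondary care, CHESS or ONS mortality as a route. No other section of the article adds one.

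**2. The plan's own event chain (Sample size section)**

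- Infected: 1 400 000 × 0.062 = 86 800 (stated: 86 600).
- Diagnosed: 86 600 × (1 − 0.63) = 32 042 (as stated).
- Hospitalised: 32 042 × 0.25 = 8 010 (stated: 8000).
- Deaths: 32 042 × 0.064 = 2 051 (stated: 2050).

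The chain reproduces. It takes every hospitalisation and death as a share of diagnosed cases, a nesting that Table 3 does not guarantee.

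**3. Diagnoses missed**

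Let f be the share of COVID-19-coded admissions with no qualifying diagnosis record. The documents do not give f; 5% to 20% is an assumption. Missed = f × 8 010; share = missed / 32 042.

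- f = 5%: 400, or 1.2%.
- f = 10%: 801, or 2.5%.
- f = 20%: 1 602, or 5.0%.

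If f is read as the share without a linked swab only, these are upper figures for the broad outcome, because an app report or a GP code would still rescue some workers. Deaths coded without an admission are not included.

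**4. Effect on the diagnosis incidence rate ratio**

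Assume that 35% of minority cases and 25% of White cases are hospitalised. The 25% is the plan's overall rate; the 35% is assumed. With the same f in both groups, the observed ratio is the true ratio times (1 − 0.35f) / (1 − 0.25f).

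- f = 5%: 0.9825 / 0.9875 = 0.995.
- f = 10%: 0.965 / 0.975 = 0.990.
- f = 20%: 0.930 / 0.950 = 0.979.

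The bias is about 0.5% to 2%, towards the null if the true ratio exceeds 1.

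**5. What the swab-only subgroup leaves out**

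If the same f applies to deaths, fatality among swab-confirmed cases is 2 050(1 − f) / (32 042 − 8 010f). This gives 6.2%, 5.9% and 5.4% at f = 5%, 10% and 20%, against 6.4%. If only the unswabbed deaths are removed, and f is 5% in one ethnic group and 10% in another, a true mortality risk ratio of 1.00 appears as [0.064 × 0.90 / (1 − 0.064 × 0.10)] / [0.064 × 0.95 / (1 − 0.064 × 0.05)] = 0.95. With the groups exchanged it appears as 1.05.

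**The case against.** The strongest reply is that a swab-only definition of confirmed diagnosis is a legitimate high-specificity choice, and that Pillar 1 is the hospital testing stream, so most U07.1 inpatients should be confirmed wherever testing data link. Both points stand. A U07.2 case is rightly not confirmed. What remains is its absence from the broad outcome, together with U07.1 cases that have no linked test.

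A reader might infer more than the documents support:

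- **That confirmed diagnosis should itself be widened, or that unswabbed inpatients should enter the confirmed-case mortality subgroup.** This would admit unswabbed workers only because they were ill enough to be admitted. That is selection on severity, in a study whose Discussion already warns of collider bias.
- **That poor swab linkage is expected in some countries, which are then pooled with better ones.** The article says that whole outcome data sets may be unobtainable in a country, and that countries are therefore analysed separately before meta-analysis. It does not describe graded linkage quality.
- **That the Outcome incidence section claims diagnosis contains all later events.** It refers to preceding events in general, and Table 3 lists three separate mortality subgroups.
- **That these workers vanish from the mortality analyses.** They stay in the whole-cohort analyses and, if admitted with a code, in the COVID-19 hospitalisation subgroup.
- **That the confirmed-case mortality hazard ratio is shown to be biased.** The figures in step 5 of the working need an assumed f, and the relative one also needs an assumed ethnic difference in f. No hazard ratio can be derived from the documents.

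The Discussion concedes that undiagnosed, mild and asymptomatic infections are missed. It does not address severe cases that hospital or death records already identify.

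**Conclusion.** The point holds for the broad diagnosis outcome. As written, Table 3 counts some COVID-19 admissions and deaths as neither confirmed nor suspected, and for those workers the interval from diagnosis to outcome does not exist. That contradicts the purpose of having a broad outcome.

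The size is modest and uncertain. Under the assumed 5% to 20%, about 400 to 1,600 of 32 042 diagnoses are missed, and the diagnosis rate ratio shifts by about 0.5% to 2% under the assumed hospitalisation contrast. Both ranges rest on assumptions, and both are small beside the 63% of infections that the plan already takes to be undiagnosed. The change is worth making because it is nearly free and removes an internal inconsistency, not because a large bias has been shown.

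**What to change.** 1. In Table 3, add U07.1 or U07.2 on a hospital, ITU or death record in the study period to the suspected row, with secondary care, CHESS and ONS mortality as sources. Such a record then counts in the combined confirmed-and-suspected diagnosis, dated at the earliest qualifying record.
2. Keep confirmed diagnosis swab-only, and keep swab-based entry for every confirmed-case subgroup (hospitalisation, ITU, mortality).
3. Report the number of coded admissions and coded deaths without a linked positive swab, by ethnic group and country. This replaces the assumed f with an observed one and makes the loss from the confirmed-case mortality analysis visible.

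**Cost:** a change of wording in Table 3 and a little programming; the sources are already planned for linkage. Some miscoded records will enter the broad outcome, and the confirmed-only outcome already planned alongside it will show their effect. Workers first identified by an admission or death record will have an interval of zero to that event by construction, so their number should be stated where intervals are summarised.
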